# Xue-Fu-Zhu-Yu capsule in the treatment of qi stagnation and blood stasis syndrome: a study protocol for a randomised controlled pilot and feasibility trial

**DOI:** 10.1186/s13063-018-2908-9

**Published:** 2018-09-21

**Keywords:** Xue-Fu-Zhu-Yu capsule, Qi stagnation and blood stasis syndrome, Chinese medicine, Randomised clinical trial

## Abstract

**Background:**

Qi stagnation and blood stasis syndrome (QS&BSS) is one of the common *Zhengs* in traditional Chinese medicine (TCM), which manifests as various symptoms and signs, such as distending pain or a tingling sensation in a fixed position. In recent years, a number of clinical trials have focused on the effectiveness and safety of XFZYC in patients with a QS&BSS subtype disease, such as coronary heart disease, hyperlipidaemia, ischaemic cerebrovascular disease, gastritis, dysmenorrhoea, or arthritis, in terms of the outcomes of relevant diseases. However, there is lack of evidence of the effects of XFZYC in patients with QS&BSS with different diseases, focusing on the outcomes of *Zhengs*.

**Methods/Design:**

A randomised, controlled, pilot and feasibility trial will be employed in this study, using a 7-week study period. Participants will be recruited from Guang’anmen Hospital, Huguosi TCM Hospital, Wangjing Hospital in China. One hundred and twenty participants will be randomised to a treatment group (Xue-Fu-Zhu-Yu Capsule (XFZYC)) and placebo group in a 1:1 ratio. Participants included in the study must be diagnosed with Qi stagnation and blood stasis syndrome criteria. The outcome measurements will include the traditional Chinese medicine patient-reported outcome (PRO) scale for QS&BSS, the single symptom and sign scale of QS&BSS, and the pain scale of QS&BSS. The clinical data management system (http://www.tcmcec.net/) will be used to collect and manage the data. Quality control will be used, according to Good Clinical Practice (GCP).

**Discussion:**

Previous studies were expected to evaluate whether the addition of XFZYC to standard routine treatment would enhance the treatment effectiveness and improve the biomedical parameters pertaining to relevant disease. However, this trial is focused on the outcome of *Zhengs*, and we chose a range of outcome measurements to assess the improvement of relevant symptoms and signs. This trial is the first study designed to define and optimise the outcome measurements of *Zhengs* of XFZYC in the treatment of patients with QS&BSS.

**Trial registration:**

ClinicalTrials.gov, NCT03091634. Registered on 12 August 2018. Release date 6 May 2017.

**Electronic supplementary material:**

The online version of this article (10.1186/s13063-018-2908-9) contains supplementary material, which is available to authorized users.

## Background

Traditional Chinese medicine (TCM) has experienced a long history and shaped its own theory. Within the framework of TCM theory, TCM practitioners always prescribe herbal medicines and acupuncture formulae based on specific diseases and *Zhengs* [1]. What are *Zhengs*? They can be not only a subtype disease but also a type of common symptom occurrence of different diseases. Specifically, TCM practitioners always identify *Zhengs* by recognising a slight difference in the same symptoms of the same disease. For example, chest pain is a common symptom of coronary heart disease, but this symptom could be divided into several subtypes based on the description of the pain experienced. Distending pain and stabbing pain are regarded as one subtype and type of *Zhengs*, which is named Qi stagnation and blood stasis syndrome (QS&BSS, also known as Qi-Zhi-Xue-Yu Zheng) and is treated differently from other *Zhengs*. In this way, the differentiation of *Zhengs* makes TCM treatment become individualised in some sense. On the other hand, when specific similar symptoms arise in various diseases, patients with different diseases could be treated by the same TCM therapy according to the theory of TCM, which has been accepted by the Consolidated Standards of Reporting Trials (CONSORT) for Chinese Herbal Medicine Formulas 2017 [2]. For instance, distending pain and stabbing pain in some cases might be one of the main symptoms of stable angina, stomach ache, dysmenorrhoea and other conditions. Therefore, this common symptom in different diseases could receive a complementary treatment using the same TCM therapy. Although this treatment approach allows TCM formulae to have a wide range of application and has been employed by TCM doctors for thousands of years, more specific evidence should be accumulated to support this type of approach and its underlying theory.

From the perspective of TCM, Qi and blood are considered to be the fundamental substances constituting the human body, and the material basis for human health and diseases. Therefore, QS&BSS is one of the common *Zhengs* in TCM and manifests as various symptoms and signs, such as distending pain or a tingling sensation in a fixed position, irritability or depression, dim complexion, lumps on the body, blood spots under the skin, unsmooth or string-like pulse, and purplish tongue or petechiae on the tongue. In fact, Qi stagnation and blood stasis are common pathological conditions that occur in the human body several times in a human’s life. Moreover, QS&BSS is associated with over 50 diseases, including coronary heart disease, hypertension, cerebral infarction, gastritis, arthritis, dysmenorrhoea, chronic pelvic infection, skin disease, and cancer [3–11].

There are several types of TCM therapies that are used for treating QS&BSS, including Chinese herbal medicine (CHM), acupuncture, moxibustion, cupping, massage and Qigong therapy. Xue-Fu-Zhu-Yu Capsule (XFZYC), one of the Chinese herbal medicine (CHM) drugs, could perform the function of promoting Qi and activating blood to relieve the symptoms of QS&BSS; its use was approved by the China Food and Drug Administration (CFDA) in 2002. The components of the capsule include the following: *Radix Bupleuri* (chaihu), *Angelica Sinensis* (danggui), *Radix Rehmanniae Recens* (shengdihuang), *Radix Paeoniae Rubrathe* (chishao), *Carthamus Tinctorious* (honghua), peach kernel (taoren), *Fructus Aurantii* (zhiqiao), *Radix Liquiritiae* (gancao), *Ligusticum Wallichii* (chuanxiong), *Radix Achyranthis Bidentatae* (niuxi), and *Platycodon grandiflorum* (jiegeng). XFZYC has been used for the treatment of QS&BSS since it was recorded in the book *Correction on Errors in Medical Classics* 200 years ago. In recent years, a number of clinical trials have focused on the effectiveness and safety of XFZYC in patients with QS&BSS subtype diseases, such as coronary heart disease, hyperlipidaemia, ischaemic cerebrovascular disease, gastritis, dysmenorrhoea, and arthritis [5, 7, 8, 12–14], in terms of the outcomes of relevant diseases. However, evidence for the use of XFZYC to address the *Zhengs* in patients with QS&BSS is lacking. To define and optimise an outcome design for a future, adequately powered, definitive trial to evaluate the effectiveness and safety of XFZYC in the treatment of QS&BSS, a multicentre, randomised pilot trial will be undertaken.

## Methods/Design

### Trial objective

The primary objective of this trial is to assess the acceptability and feasibility of the outcome measures as methods to evaluate the effectiveness of the CHM in terms of *Zhengs* within definitive trials.

### Research design

This study is a multicentre, prospective, double-blind, randomised, controlled pilot trial. This study design follows the international recommendations for interventional trials (see the standard protocol items: recommendation for interventional trials (SPIRIT) checklist in Additional file 1). Additional file 2 provides a brief overview of our design. This pilot and feasibility trial will be reported using the CONSORT 2010 statement extension for randomised pilot and feasibility trials as a reference [15].

### Registration

The trial was registered at Clinical Trials.gov (ID, NCT03091634). The study will be conducted in compliance with the Declaration of Helsinki and Good Clinical Practice (GCP) guidelines.

### Settings and participants

We will recruit participants in two ways. First, the study information will be advertised on hospital notice boards and the WeChat application programme, and interested participants can register for this trial by telephone with the researcher or through WeChat. Second, the clinical staff at outpatient clinics will scan and identify potential participants who will then be approached with the study information. These two methods will be followed up by a screening visit with the researchers. A total of 120 patients will be enrolled at one of the following three hospitals in Beijing, China: (1) Guang’anmen Hospital, China Academy of Chinese Medical Sciences, (2) Huguosi TCM Hospital, Beijing University of Chinese Medicine, and (3) Wangjing Hospital, China Academy of Chinese Medical Sciences.

### Diagnostic criteria

#### Traditional Chinese medicine diagnostic criteria for QS&BSS

To avoid the subjectivity associated with expert syndrome differentiation, a traditional diagnostic method, both TCM syndrome differentiation diagnostic criteria for QS&BSS and the TCM syndrome diagnostic scale for QS&BSS will be used in the trial. A diagnosis of QS&BSS should satisfy the following three TCM diagnostic criteria simultaneously:Expert syndrome differentiation: two deputy chief physicians will make an independent diagnosis by syndrome differentiation. If the patient is diagnosed as having QS&BSS by both physicians, he/she could be enrolled. If the diagnosis is different between the two physicians, another deputy chief physician will contribute to the final diagnosis.TCM syndrome differentiation diagnostic criteria for QS&BSS: primary symptoms and signs are (1) distending pain; (2) tingling sensation; (3) pain in a fixed place; (4) pain aggravated by touch; (5) lumps in the body; (6) irritability; and (7) depression.Secondary symptoms and signs are (1) loss of appetite; (2) dim complexion; and (3) blood spots under the skin. Tongue manifestation involves (1) purplish tongue and (2) petechiae on the tongue.Pulse condition involves (1) unsmooth pulse and (2) string-like pulse.A diagnosis of QS&BSS should include more than two primary symptoms and signs; more than one secondary symptom and sign; and one tongue presentation or pulse presentation.TCM syndrome diagnostic scale for QS&BSS: the TCM syndrome diagnostic scale for QS&BSS will be used to assist with the diagnosis. When the total score is greater than or equal to 20, the patient could be diagnosed with QS&BSS (See Additional file 3: Table S1).

#### Disease diagnostic criteria

The diagnostic criteria for coronary heart disease are based on the guidelines for the diagnosis and management of patients with stable ischaemic heart disease (2012) [16]; chronic gastritis is based on the consensus of chronic gastritis in China (Shanghai, 2012) [17]; cerebral infarction is based on the guidelines for the early management of patients with acute ischaemic stroke (2018) [18]; dysmenorrhoea is based on primary dysmenorrhoea consensus guidelines (2017) [19]; and arthritis is based on the Chinese guidelines for the diagnosis and management of osteoarthritis (2018) [20].

##### Inclusion criteria

The inclusion criteria are the following:Meets the QS&BSS criteriaOne of the five aforementioned diagnostic diseasesPatient is 18 to 65 years of ageVoluntarily provided written informed consent

##### Exclusion criteria

The exclusion criteria are the following:Diagnosis of acute myocardial infarction, acute phase of cerebral infarction, aortic dissection or other critical illnessPoorly controlled hypertension (systolic pressure > 160 mm of mercury (mmHg) or diastolic blood pressure > 100 mmHg), severe heart failure or severe arrhythmia (atrial fibrillation, atrial flutter, ventricular tachycardia, paroxysmal type II atrioventricular block and complete bundle branch block)Severe primary diseases of the heart, brain, liver, kidney, and haematopoietic system, liver function alanine aminotransaminase (ALT) or aspartate aminotransferase (AST) value > 1.5 times the upper limit of the normal value, or abnormal renal functionDepression or anxiety disordersPregnant or lactating womenNervous system conditions, mental illness, or lack of cooperation with the studySurgery during the past 4 weeksBleeding tendencies, disseminated intravascular coagulation (DIC), abnormal international standard ratio (INR) value, or thrombocytopeniaParticipation in another trial in the past 1 monthAllergies to the test drug or an allergic constitutionAphasia that affects data collectionOther obvious TCM syndrome

##### Rejection criteria

The rejection criteria are as follows:Reluctance to continue the trialUnwillingness to take the trial drugNo medical record by which to be evaluated

##### Suspension criteria

The study may be suspended for the following reasons:Non-cooperation of the participants during the trial for any reasonThe decision to suspend the study by CFDA or other authorityOccurrence of serious adverse events (SAEs)Discovery of a deviation in the protocol

### Randomisation

A total of 120 eligible participants will be allocated to either the XFZYC group or placebo group in a 1:1 ratio using a block randomisation method. The central randomisation system will be used and performed by the Clinical Evaluation Centre of China Academy of Chinese Medical Sciences, which will also maintain the randomisation lists.

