### Sample size

Due to the lack of preliminary studies on the evaluation of the efficacy of XFZYC for QS&BSS using the traditional Chinese medicine patient-reported outcome (PRO) scale, we could not calculate the appropriate sample size. Therefore, we adopted this pilot study with an appropriate sample size of 60 participants per group. The outcomes of this trial will provide data support for the calculation of the appropriate sample size for future clinical trials.

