### Data management and statistical analysis

The clinical data management system (http://www.tcmcec.net/) will be used to collect and manage the data. All data from the completed CRFs will be imported into the system twice by two independent data entry clerks to ensure the accuracy. The database will be locked when the principal investigators and statisticians check the data. The original medical records will be archived and saved in the unit responsible for 5 years after the completion of the trial.

All statistical analyses will be performed by an independent statistician blinded to the allocation, using the Statistical Analysis System (SAS, Version 9.2, Institute Inc., Cary, NC, USA) and assuming a two-sided test and a 0.05 level of significance. Based on the strict principle of intention-to-treat (ITT), the outcome measurements will be analysed using a full analysis set (FAS), which means the data of the participants will be analysed according to their original allocation, regardless of the treatment they actually received, withdrawals, losses to follow up, or crossovers. The last-observation-carried-forward (LOCF) method will be used for missing data, and safety outcomes will be analysed using safety sets (SS). Quantitative data will be analysed using the *t* test and analysis of variance (ANOVA). Enumeration data will be analysed using the chi-square test or non-parametric tests. We will use the paired *t* test to analyse significant differences between pre and post treatment. The total dropout rate in each group will be analysed using the chi-square test or Fisher’s exact test. Moreover, the reasons for dropouts will also be descriptively analysed and compared between the two groups. For the safety analysis, the incidence rate of adverse events will be evaluated using the chi-square test and described in a list.

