### Quality control

Quality control will be performed as followsRequest for the investigators:

The investigators must possess the qualifications and abilities needed to conduct the trial and will not be continually changed. The principal investigators will ensure the trial is conducted according to the standard operating procedure. A project manager at each site will be responsible for the quality of the research.2.Quality control throughout the entire process of the trial:

Before the trial, investigators will receive pre-trial training on patient screening, data filling, drug use, adverse event (AE) reporting and other matters. During the trial, the investigators will confirm that the participants have received the drugs on time and record the receipt on the medication record form. Those patients who do not take the drugs at the appropriate time will be encouraged to do so, and their reasons will be recorded in detail. Trial supervisors will visit each site regularly to check the case report forms and informed consent to ensure that the trial is strictly following the protocol. The investigators will take measures (to schedule further visits and follow-ups) to keep the incidence rate of dropout within 20%. The number of withdrawals, dropouts, and cases of compliance will be recorded in detail. The trial data will be entered into the database within 2 weeks of being collected. After the trial, all the data will be checked by the quality controller, principal investigator, and statisticians [2].

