## Discussion

The research design of a previous study pertaining to XFZYC was characterised by the objectives of patients with QS&BSS with only one simple disease, and they were expected to evaluate whether the addition of XFZYC to the standard routine treatment would enhance the effectiveness and improve the relevant biomedical parameters. However, this trial is focused on the outcome of *Zhengs*, and we chose the PRO scale of QS&BSS to assess the improvement of relevant symptoms and signs. We will also compare the outcomes among different diseases by subgroup analysis. When the evidence accumulates to a certain degree that supports this treatment approach and theory, TCM complementary and alternative treatments will be available to a wider range of the world’s population and will be more pragmatic and standardised.

What might be the mechanism underlying the use of XFZYC for patients with different diseases? To date, several studies have found that QS&BSS was associated with traits such as haemodynamics, haemorheology, neuroendocrine function, vascular endothelial cells, blood lipids, inflammatory substances, genomics, proteomics, and metabolomics, which manifest with a decrease in peripheral vascular compliance and tissue plasminogen activator (t-PA) activity, an increase in plasma neuropeptide Y and tumour necrosis factor-α (TNF-α), interleukin-6 (IL-6), a change in the expression of microR-7641 and micR-4484, plasma protein CD44SP, or a change in the metabolism of glucose, arachidonic acid and linoleic acid [3, 25–30]. Based on the biological essence of the *Zheng* of QS&BSS, other studies have illustrated that XFZYC enhances anti-atherogenic activity, improves cardiac microcirculation, prevents platelet aggregation, modulates angiogenesis, potentiates t-PA, reduces inflammatory markers, and offers neuroprotection [31–36]. We can infer that QS&BSS may be related to the common pathogenesis of several types of diseases that might be treated by XFZYC.

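### Five diseases from three hospitals are pooled, but the stated between-arm analysis has no disease or hospital term and the published allocation names no stratum; adjusting for both costs almost nothing

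*Protocol article*

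**What the plan says.** All references are to the protocol article.

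- **Randomisation:** the 120 participants "will be allocated to either the XFZYC group or placebo group in a 1:1 ratio using a block randomisation method". The section adds that "The central randomisation system will be used and performed by the Clinical Evaluation Centre of China Academy of Chinese Medical Sciences". It gives no block size and no stratification factor, and no other section names one.
- **Settings and participants:** "A total of 120 patients will be enrolled at one of the following three hospitals in Beijing".
- **Disease diagnostic criteria and Inclusion criteria:** a participant needs one of coronary heart disease, chronic gastritis, cerebral infarction, dysmenorrhoea or arthritis. There is no quota or expected number for any of them.
- **Discussion:** "We will also compare the outcomes among different diseases by subgroup analysis".
- **Data management and statistical analysis:** quantitative data are compared by t test and analysis of variance, "assuming a two-sided test and a 0.05 level of significance". No factor other than treatment is mentioned.
- **Sample size:** "we adopted this pilot study with an appropriate sample size of 60 participants per group". No calculation underlies this number, and the results are meant to feed the sample size of a later trial.

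**The concern.** The five diseases plausibly differ in the level and course of pain and symptoms. They also differ in background care, because the Intervention section lets prior routine treatment continue. As published, neither the allocation nor the analysis takes disease into account.

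Two things follow if that is the whole plan. First, variation between diseases stays in the error term of the between-arm comparison and in the SD that the pilot hands on. Second, blocks over the whole trial balance the arms overall but not within a disease, so the planned comparison among diseases may rest on uneven arms. The first matters more, because supplying data for the next sample size is a stated purpose of the trial.

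**Working it through.** **The plan's own figure.** 120 / 2 = 60 per group, which agrees with the Sample size section. No effect size, SD or power is given, so nothing further can be reproduced.

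**Inputs from the article:** 120 participants, 1:1, block randomisation, five diseases, three hospitals.

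**Assumptions (not in the article):** participants per disease, block size, differences between disease means, and, for step 3, allocation without strata.

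**1. Residual variance when disease is left out.** Take 24 per disease, within-disease SD 1 and disease means -0.8, -0.4, 0, 0.4, 0.8.

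- Between-disease variance = (0.64 + 0.16 + 0 + 0.16 + 0.64) / 5 = 0.32.
- Unadjusted variance = 1 + 0.32 = 1.32; SD = √1.32 = 1.15.
- Required sample size is proportional to variance, so one planned on the unadjusted SD is about 32% larger than one planned on the disease-adjusted SD.
- With means half as far apart (-0.4 to +0.4), the between-disease variance is (0.16 + 0.04 + 0 + 0.04 + 0.16) / 5 = 0.08, an inflation of 8%. With equal means it is zero.

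Stratifying the allocation does not change this SD. In 5,000 simulated trials under the first set of means, the pooled within-arm SD averaged 1.148 without strata and 1.150 with strata.

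**2. Effect on the overall arm difference (same means).**

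- SD due to disease mix alone = √(0.32 × 2/60) = 0.10.
- Total SD without strata or adjustment = √(1.32 × 2/60) = 0.21 (simulated 0.211).
- SD with disease balanced = √(1 × 2/60) = 0.18 (simulated 0.184 with stratified blocks).
- The unadjusted t test uses a standard error of about 1.15 × √(2/60) = 0.21 in both cases. That is right for unstratified allocation and too large for stratified allocation, so the disease term is needed either way.

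**3. Imbalance within a disease if there are no strata.** For 24 of 120, the number in one arm has variance 24 × 0.5 × 0.5 × (120 - 24)/(120 - 1) = 4.84, SD 2.2. A 16:8 or worse split is a departure of at least 4 from 12. Simulation (20,000 trials per scenario, blocks of 4) gives:

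| Assumed disease sizes | At least one disease 2:1 or worse | At least one 3:1 or worse |
|---|---|---|
| 24 in each | 40% (about 11% per disease) | 5% |
| 40/30/20/20/10 | 46% | 14% |
| 50/30/20/12/8 | 59% | 38% |

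Blocks of 6, or one block of 120, give almost the same results.

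**4. What imbalance costs.** Efficiency relative to an even split is 4ab/n², for a and b participants per arm and n = a + b.

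- 16:8 gives 4 × 128/576 = 89%; 18:6 gives 4 × 108/576 = 75%.
- Mean efficiency is about 97% at n = 24, 91% at n = 10 and 88% at n = 8.
- For an assumed difference of 0.8 SD in a disease of 24, power is 50% at 12:12, 46% at 16:8 and 40% at 18:6.

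So adjusting for disease after unstratified allocation still gains a factor of about 1.32 × 0.97 = 1.28 in precision. Stratifying as well recovers the remaining 3%.

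**The case against.** The best reply is that a journal article condenses a fuller protocol and that model terms are commonly left to the analysis plan. This largely stands for allocation. A reader might infer that randomisation is unstratified, but the article does not say so; it is silent, and a central system could hold strata. It stands in part for the analysis. ANOVA is listed and could include disease, but the article names no such factor, and the t test beside it has none. If the full documents specify both, the point is answered.

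Four stronger readings are tempting and unsupported:

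- **That arms within a disease will be badly unbalanced.** At 24 per disease the average loss is about 3%. The description fits only groups of roughly 8 to 12, which are too small to say much even when evenly split. In general, subgroup size limits the disease comparison more than imbalance does, and stratification does not cure that.
- **That the comparison is biased.** Chance imbalance is random error. It does not bias a contrast within a disease, and for the overall contrast the t test's standard error already reflects it.
- **That uneven allocation inflates the SD handed on.** Step 1 shows that it does not; omitting disease from the analysis does.
- **That the trial's main aim is at risk.** The primary objective is feasibility and acceptability of the outcome measures, with a data-completeness threshold. Arm balance within a disease does not enter it.

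The hospital part is weaker than the disease part, since no comparison by hospital is planned. Stratification also comes late: recruitment began on 6 May 2017, completion is due by December 2018, and the article appeared in September 2018.

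**Conclusion.** The point holds as a low-cost improvement to the stated analysis. The trial deliberately mixes five diseases and intends to compare them, yet the between-arm comparison as written ignores disease and hospital. The gain from adjusting depends on how far disease means differ, which the article does not tell us: about 32% in residual variance under the wider assumption, 8% under the narrower, none if the means are equal. Possible imbalance within diseases is secondary. It arises only if allocation is in fact unstratified, and it has a 40% to 59% chance of a 2:1 or worse split in at least one disease over the mixes tried. Its cost is small except in small disease groups.

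**What to change.** 1. Replace the unadjusted between-arm t test with a linear model containing treatment, qualifying disease and hospital. Disease is established at entry and hospital is known, so no new data are needed. The cost is 4 + 2 = 6 degrees of freedom, leaving 120 - 8 = 112 instead of 118 with complete data.
2. Report the disease-adjusted residual SD as the figure for planning the definitive trial.
3. State whether disease and hospital are strata in the central system. If disease is not, stratify any remaining allocation by disease. Blocks of 4 within disease limit the arm difference in that disease to 2. Do not cross disease with hospital, which would make 5 × 3 = 15 cells for 120 participants. The cost is a system setting and, because of incomplete blocks, totals that may differ slightly from 60:60.

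For participants already allocated, the first two steps are sufficient.
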